| 4.4 | **Description of measures taken to reduce and avoid analysis biases:**  Any validation raises methodological bias that are difficult to address. One of the questions investigators can act on is the inter-judge subjectivity for coding. Indeed, faced with varied profiles children with atypical behavior (which are sometimes very difficult to interpret), the quotes can vary from one judge to another. To avoid this analysis bias, an objective analysis grid will serve as a guide and a double coding will be done on the evaluation records. Thus we will proceed to a calculation of kappa coefficient to see the degree of agreement between several judges.  A key question that arises is: what to attribute a significant difference to? In two years, young children with autism change a lot, as do all children: longitudinal follow-ups indicate that children with the same initial profile diverge, with some of them making great progress while others stagnate or even regress (Pry & Darrou , 2009). To resolve this proble, since a control group could not be constituted, the evolution will be compared to the data available in the literature, notably (if possible) ongoing study also using PEP, CARS, Vineland and ADI-R (search workshop-class Preaut). It will take a massive superiority of the results of the method of 3I to be attributed as such the success eventually achieved. |
| **4.5** | **Detailed description of how to use the device:**  The implementation of the device assumes:  - The equipment of the 3I game room (file AEVE1 DEC1 PJ2)  - Research and selection of non-professional workers, mentioned in 2.1.d (there is usually a great diversity of stakeholders, each of whom brings to the child a way to play and their own aptitudes and interests most of them are women)  - The choice of a psychologist having the approval for a 3I care,  - The organization of the weekly schedule of the volunteers,  - The game in turn session in individual with the child,  - The note taking by the volunteer on the course of his session, with the possible mention of passages to be reviewed by the psychologist,  - The weekly session of the child with the psychologist,  - Holding of the monthly meeting of experience sharing, evaluation according to the developmental evaluation grid 3I skills and know-how, (file AEVE1 DEC1 PJ3) allowing a sharing of feeling and experience and to identify progress to be encouraged. |

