| **7.2** | **Methods and schedule for measuring, collecting and analyzing evaluation parameters:**  The quantitative methods used to measure performance changes will consist in comparing the results obtained at the different assessments at different periods of care (T + 1 month, T + 12 months, T + 24 months). The collection and analysis of intermediate data will be carried out progressively as the evaluations are carried out. The first analysis will be conducted at the end of the second evaluation period (T + 12 months), we will compare the data from all these tests, at T + 1months. period T + 12 months. A second analysis will be conducted at the end of the tests to compare the performance of the method between the three measurement periods (T + 1 month vs. T + 12 months vs. T + 24 months).  Through PEP-R (Schopler, 2005), we will conduct a performance analysis based on an assessment and direct observation of the child. The analysis will focus on two types of data collected: 1) the age of global and specific development corresponding to different areas of development (Imitation, Perception, fine motor skills, gross motricity, hand-hand coordination, cognitive performance, verbal cognition) and And 2) behavioral observations (relationships and affect, play and interest in the material, sensory responses, and language) collected during the assessment sessions. This tool, which gives a global and specific level of development for each evaluated domain, makes it possible to see the homogeneity of the development. The more the development becomes homogeneous during the 2 years of care, the better the performance of the 3I method.  Via the Scale of Imitation (Nadel, 2012), we will perform a detailed analysis of socio-communicative skills. This tool makes it possible to evaluate the level of the preverbal communication, in particular that of the imitation. It consists of three scales: spontaneous imitation, recognition to be imitated and imitation on request. The analysis of the scores obtained in these three sub-scales will make it possible to better follow the effect of this method on the development of nonverbal communication in very young or non-verbal subjects. An analysis of socio-emotional behavior (CPSE) based on a behavioral coding grid will measure the impact of the 3I method on the evolution of social-emotional behaviors (positive vs. negative). The higher the imitation scores and the number of positive social-emotional behaviors increase over the 2 years of care, the better the 3I method's performance.  These tests will be accompanied by 3 semi-structured interviews with parents (ADI-R, CARS, VABS). These are multidimensional assessments of learning and dysfunctions in everyday life.  The ADI-R which is a diagnostic assessment tool focuses on the description and history of child development in the three domains: quality of social interactions, communication and language, narrow interests and stereotyped behaviors. A change in scores on this parent questionnaire might reflect the impact of the method.  CARS, which is also a diagnostic tool, will allow us to assess the intensity of autistic disorders and their evolution during the trial. The 15 domains usually disturbed in autism are evaluated there: social relations, imitation, emotional response, use of the body, use of objects, adaptation to change, visual responses, auditory responses, taste-smell-touch (responses and modes of exploration), fear and anxiety, verbal communication, nonverbal communication, level of activity, intellectual level and homogeneity of intellectual functioning and general impression. The lower the overall score during trail, the better the performance of the 3I method.  The VABS which is a social adaptation assessment tool makes it possible to analyze, through the scores converted into developmental age (referred to mean equivalent ages of the normal sample), the impact of the 3I method on the development of socialization, communication, and the autonomy of everyday life. The more the difference between the chronological age of the subject and his age of development decreases during the management, the better the performance of method 3I. |

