| **8** | **Security assessment**  The 3I method is carried out in a family setting, with the exception of the center of Lud'éveil Courbevoie for five children. Child safety is ensured mainly by his parents. The equipment in the playroom provides a camera through which all sessions can be viewed.  The risk of exposure to pedophilia by volunteers is not to be neglected; it is lessened by the presence of another person in the immediate vicinity of the playroom, and by the recording of the camera, which any interruption would raise the mistrust of the parents.  The occurrence of any events or adverse effects, within the meaning of § 5.3 will be notified by the 3I psychologist assigned to the child to the investigator. |
| **9** | **Statistisques :** |
| **9.1** | **Description of planned statistical methods and timing of interim analyzes:**  Statistical methods: It will compare the mean of the scores or the ages of developments of the cohort obtained with the different tests of the evaluation carried out at T0, T1, T2. Once the conditions of application of the parametric tests are verified we will apply a general linear mixed model (GLMM) to obtain a better statistical power while taking into account the individual variations of the subjects (subject effect). Additional analyzes will take into account the age group of the child in covariate, as well as the severity of the disorders, and the level of language (evaluated at Vineland). Individual studies may be carried out.  Independent variable:  • Time: evaluation at T0, T1, T2  Dependent variables for each test:  • CARS: total score  • VABS: age of development by domain (4)  • PEP-R: overall development age, age of development by domain (7) IMITATION: score by domain (3), number of socio-emotional behavior (positive vs negative)  In addition, we will analyze the profiles of each subject to evaluate areas of evolution (case study).  Calendar of interim analyzes:  • Intermediate analysis on T1 tests compared to T0  • Final analysis on T2 tests compared to T0 |
| **9.2** | **Expected number of subjects to include and statistical justification:**  About 20 subjects in the experimental group 2 years-12 years to perform parametric tests. |
| **9.3** | **Degree of signification:**  The main effects and interactions will be considered significant if the p-value is lower than the risk α = 0.05 |

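### Section 9.1 tests raw developmental age against zero change, so maturation alone is likely to near-certain to give significance, and the metric conflicts with section 7.2

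*Protocol*

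**What the plan says.** Protocol section 9.1 describes the efficacy comparison: "It will compare the mean of the scores or the ages of developments of the cohort obtained with the different tests", at T0, T1 and T2, using a general linear mixed model. The only independent variable is "Time: evaluation at T0, T1, T2". The dependent variables include developmental age in each of four VABS domains, and PEP-R developmental age overall and in seven domains. Age group, severity and language level enter only in additional analyses. Section 9.3 sets the significance level at 0.05, and section 4.3 looks for significant improvement in the observed scores. Section 4.1.1 makes VABS communication and socialization main criteria, together with the imitation scale.

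Section 7.2 reads VABS differently: "The more the difference between the chronological age of the subject and his age of development decreases during the management, the better the performance".

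Section 4.4 recognises the maturation problem: "In two years, young children with autism change a lot, as do all children". It says that no control group could be formed, turns to literature data (one ongoing study only if possible), and sets the bar for attribution: "It will take a massive superiority of the results of the method of 3I". Section 9 contains no analysis that makes this comparison.

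**The concern.** Developmental age is expressed in months and rises as a child grows older, even when development is well below the normal rate. A test of whether its mean differs between T0 and T2 therefore asks whether the children developed at all, not whether they developed faster than they otherwise would have. The main objective in section 3 is the effectiveness of 3I, and two of the main criteria are analysed on this scale.

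Two things are at stake. First, a significant result on VABS communication or socialization would be expected for an ineffective method. Second, 9.1 and 7.2 can disagree on the same child, so the reader cannot tell which metric decides whether VABS improved. The step that is meant to separate 3I from maturation, the comparison in 4.4, has no place in the statistical section.

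**Working it through.** **Inputs from the Protocol.** About 20 children in one group (9.2); alpha 0.05 (9.3), taken as two-sided because the side is not stated; T0 at 1 month and T2 at 24 months of care (7.2), so the interval is 24 − 1 = 23 months. Section 9.2 gives no effect size, SD or power, so there is no figure of the plan's own to reproduce.

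**Assumptions, since the Protocol gives neither.** Natural rate r, in developmental months per calendar month, from 0.2 to 1.0 with zero effect of 3I. SD of individual change from 6 to 15 months. A paired t-test of T2 against T0 stands in for the mixed-model time contrast.

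**Step 1: what maturation alone produces on the 9.1 scale.** Mean gain = r × 23. Noncentrality = gain / SD × √20. The critical value is t(0.975, 19 df) = 2.093. For example, with r = 0.5 and SD 15, the gain is 11.5 and the noncentrality is 11.5 / 15 × 4.472 = 3.43, which gives a probability of 0.90.

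Probability of a significant increase with zero 3I effect:

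| r | Mean gain (months) | SD 6 | SD 9 | SD 12 | SD 15 |
|---|---|---|---|---|---|
| 0.2 | 4.6 | 0.90 | 0.58 | 0.37 | 0.26 |
| 0.3 | 6.9 | 0.998 | 0.90 | 0.68 | 0.50 |
| 0.5 | 11.5 | 1.00 | 1.00 | 0.98 | 0.90 |
| 0.7 | 16.1 | 1.00 | 1.00 | 1.00 | 0.995 |
| 1.0 | 23.0 | 1.00 | 1.00 | 1.00 | 1.00 |

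The smallest mean gain that reaches p<0.05 is 2.093 × SD / √20. That is 2.8 months at SD 6 and 7.0 months at SD 15, or 0.12 to 0.31 of the normal rate over 23 months.

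**Step 2: 9.1 against 7.2.** A child at a constant half rate gains 0.5 × 23 = 11.5 months, which is improvement under 9.1. The gap to chronological age widens by (1 − 0.5) × 23 = 11.5 months, which is worse under 7.2.

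**Step 3: is the gap itself the better metric?** It removes the false positive: in simulation with no 3I effect, significant narrowing occurs in about 0.025 of trials at r = 1.0 and in fewer than 0.001 at r = 0.7 or below. But it can miss real acceleration. A child aged 48 months with developmental quotient (DQ, developmental age / chronological age) 0.5 has a gap of 24 months. At 71 months with DQ 0.6 the gap is 71 × 0.4 = 28.4 months. The gap has grown although the quotient rose.

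**Step 4: what DQ does and does not repair.** Simulation assumptions: n=20, start age 2 to 12 years, DQ SD 0.15, measurement SD 3 months, no 3I effect. If each child's natural rate is constant, mean DQ change is significantly positive in about 2.3% of trials (nominal 2.5%). If the natural rate over the 23 months exceeds the child's past average by 0.1 month per month, this becomes about 42%; at 0.2 it is about 93%. DQ therefore removes the calendar-age artefact only under a constant rate.

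**The case against.** The strongest reply is that the plan never equates p<0.05 with effectiveness. A reader might infer from 9.1, 9.3 and 4.3 that a significant time effect would count as success, but the text says only when an effect is called significant. Section 4.4 asks openly what a difference should be attributed to, and reserves attribution for superiority over literature data. That stands: the authors saw the problem, and the lack of a control group is declared. What remains is that 4.4's comparison has no counterpart in section 9, while the analysis that is written there tests raw age against zero. Comparator values and a margin may be set out in a statistical analysis plan that is not at hand, so their absence alone is not the point.

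It can also be said that 9.1, 7.2 and 4.4 are layers (test, direction, attribution) and not rival criteria. This is partly right. Section 7.2 is a graded statement of direction, not a pass mark, so it should not be read as requiring the gap to close. The mismatch that survives is between raw age in 9.1 and the gap in 7.2, for VABS.

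Finally, false significance is not guaranteed. Section 4.4 notes that some children stagnate or regress; that means a larger SD of change, and the table shows lower probabilities there. The age covariate does not rescue the test: it enters only additional analyses, and age group does not remove growth over time.

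**Conclusion.** The point holds for VABS developmental ages, including the two main-criterion domains, and for PEP-R developmental ages overall and by domain. With no effect of 3I, the T2 against T0 test is significant in about 90-100% of trials at half the normal rate and about 50-100% at 0.3 of it. At 0.2 it falls to between 26% and 90%. These figures rest on assumed rates and SDs and on a paired t-test as stand-in.

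A reader might extend this to every outcome in 9.1. The documents do not support that. CARS total is a severity score that is not scaled to age, and PEP-R behavioural observations and homogeneity do not rise automatically with age. For the imitation scale, a main criterion, a rise with maturation is plausible but the Protocol gives nothing from which to quantify it. An uncontrolled change in any of these is still not attributable to 3I, but that is the declared design limit and not this defect.

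**What to change.** - **9.1:** replace raw developmental age for VABS and PEP-R with one age-referenced metric, for example DQ. An alternative, developmental age at T2 minus that expected at the child's own T0 ratio, is not interchangeable with it: it equals chronological age at T2 × change in DQ, so older children weigh more. Choose one.
- **7.2:** state the VABS criterion on the same metric.
- **9.1:** state that the metric removes the calendar-age artefact only if the natural developmental rate is constant, and so does not by itself show effectiveness.
- **9.1 and 4.4:** carry the external comparison into 9.1 as an analysis for all main criteria, VABS and imitation included.
- **9.1 or 9.3:** state that p<0.05 for change over time shows change during care and not an effect of 3I.

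The cost is wording in 4.4, 7.2 and 9.1 (or 9.3), plus the work of fixing a comparator. Chronological age is already needed for 7.2. Fewer results will reach significance. With n=20, 80% power for an excess over a fixed reference needs about 0.66 SD, that is 4.0 months (SD 6) to 9.9 months (SD 15) over the 23 months.

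### Section 9.1 names only a subject effect; if fitted as a random intercept over three visits, it understates the T2–T0 standard error when children's trajectories diverge

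*Protocol*

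**What the plan says.** Section 9.1 states the model in one sentence: a general linear mixed model, used for its power, "while taking into account the individual variations of the subjects (subject effect"). The only independent variable listed is "Time: evaluation at T0, T1, T2". Age group, severity and language level enter in additional analyses. The calendar in the same section gives the last comparison as "Final analysis on T2 tests compared to T0".

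Section 7.2 describes the second analysis as a comparison of three periods: "T + 1 month vs. T + 12 months vs. T + 24 months". Section 9.3 sets the level: "The main effects and interactions will be considered significant if the p-value is lower than the risk α = 0.05". Section 9.2 gives the size: "About 20 subjects in the experimental group 2 years-12 years to perform parametric tests".

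Section 4.4, on sources of bias, reports from longitudinal follow-ups that "children with the same initial profile diverge, with some of them making great progress while others stagnate or even regress".

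**The concern.** In a three-visit model with time as the factor, a subject effect is ordinarily read as one random level per child. Child-specific rates of change would need a subject-by-time term, and none is named. With a random level alone, the T0–T1, T1–T2 and T0–T2 differences are assumed to have the same variance and are pooled into one error term.

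The divergence described in Section 4.4 breaks that assumption. If children progress at different rates, the spread of changes grows with the interval. The longest interval, T0 to T2, is the contrast named for the final analysis, and it is the one whose standard error the pooling understates. The study has no control group, and Section 4.4 plans to set the observed evolution against published data. A confidence interval for the two-year change that is too narrow would make a gap from that data look firmer than it is.

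**Working it through.** **Inputs from the protocol.** Visits at 1, 12 and 24 months (Sections 4.2 and 7.2), so the intervals are 11, 12 and 23 months. n = 20 (Section 9.2). Level 0.05 (Section 9.3); sidedness is not stated and two-sided is assumed.

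**Input not in the protocol.** Section 4.4 describes divergence in words only. I write the SD of the true 23-month change as k times the residual SD σ and show k from 0 to 3. This range is an assumption. Linear divergence and no mean change are also assumed.

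**No plan figure to reproduce.** The protocol gives no SD, effect size or power, and the 0.05 level is a design choice.

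**Step 1: true variance of a difference.** With child level + child slope × time + residual, a difference over Δ months has variance σ²[k²(Δ/23)² + 2]. For T2–T0 this is σ²(k² + 2).

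**Step 2: variance used by the random-intercept model.** With balanced data the pooled error averages the three pairwise variances. The mean squared spacing is (11² + 12² + 23²)/3 = (121 + 144 + 529)/3 = 264.7, and 264.7/529 = 0.5003. The model therefore uses σ²(0.5003k² + 2) for every pair.

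**Step 3: ratio of model to true standard error for T2–T0.** Ratio = √[(0.5003k² + 2)/(k² + 2)]. For k = 2 this is √(4.001/6) = 0.82.

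**Step 4: error rate.** 100,000 simulated trials per setting. The T2–T0 contrast uses the pooled error with 2 × (20 − 1) = 38 df.

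| k | True variance/σ² | Model variance/σ² | SE ratio | Type I error | Coverage of 95% CI |
|---|---|---|---|---|---|
| 0 | 2.00 | 2.00 | 1.00 | 4.9% | 95.1% |
| 0.5 | 2.25 | 2.13 | 0.97 | 5.6% | 94.4% |
| 1 | 3.00 | 2.50 | 0.91 | 7.3% | 92.7% |
| 2 | 6.00 | 4.00 | 0.82 | 10.8% | 89.2% |
| 3 | 11.00 | 6.50 | 0.77 | 13.0% | 87.0% |

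Separate simulation runs agree to within about 0.3 percentage points. As k grows without bound the ratio tends to √0.5003 = 0.71, a standard error 29% too small. At a slope SD of 10σ per year (k = 10 × 23/12 = 19.2) the simulated type I error is 16.7%.

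**Step 5: the alternatives.** The paired T2–T0 comparison with 20 − 1 = 19 df holds about 5% at every divergence tried (4.96% to 5.05% in 200,000 trials per setting). With complete data, an unstructured covariance leaves the T2–T0 variance equally free.

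**Step 6: two visits only.** If the model contains only T0 and T2, there is a single difference per child and nothing to pool. The random-intercept test is then the paired t test. A small mixed-model run (150 trials, slope SD equal to the residual SD per year) gave 4% with two visits and 10.7% with three. The same reasoning covers an interim analysis of T0 and T1.

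**The case against.** The strongest reply is that the random-intercept model is a reading and not the protocol's text. Section 9.1 names no random intercept, compound symmetry or pooled error, and it does not exclude random slopes. Individual variations could be taken to include individual trajectories. Covariance structure is often left to a statistical analysis plan, which is not at hand. This stands, and the point is therefore conditional. It is still worth raising, because the one term the protocol does name, on its ordinary reading, is at odds with what Section 4.4 says about these children.

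The final comparison may also use T0 and T2 alone, as the calendar in Section 9.1 could be read. The problem then disappears. Section 7.2 points to three visits, so the text leaves this open.

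Section 9.1 makes the model conditional on checking the requirements of parametric tests, and Section 9.3 mentions interactions. Neither closes the gap: equality of the difference variances is not named among the checks, and interactions with the listed covariates are not child-specific slopes.

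Three stronger inferences are tempting, and the documents do not support them:

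- **The plan as written fails to hold 5%.** This would need the random intercept and the three-visit contrast both to be fixed in the text. Neither is.
- **The interim look, or the T1 stopping criterion in Section 9.4, loses sensitivity.** In a three-visit model the T1–T0 contrast does become conservative. But Sections 7.2 and 9.1 describe the first analysis as T1 against T0, and with those two visits it is a paired test that holds 5%.
- **The subject effect was preferred to random slopes for the sake of power.** The remark about power explains the use of a mixed model; the protocol does not discuss that other choice.

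Finally, Section 4.4 does not let a significant two-year change count as success by itself. It asks for massive superiority over published results. That limits the weight of the p-value, but not the need for a correct interval around the mean change.

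**Conclusion.** The point holds conditionally. If the subject effect is a random intercept in the three-visit model, and children diverge as Section 4.4 says, the T2–T0 standard error is about 3% to 23% too small for k between 0.5 and 3, and the type I error is about 5.6% to 13% instead of 5%. Direction and limit (29%) follow from the visit spacing. The size in this trial cannot be derived from the protocol, because it gives no variances, and it is small when divergence is small.

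Confidence is high in the mechanism and medium overall, because the reading of Section 9.1 is open. The change is worth making: it costs little and protects the level in Section 9.3 whatever the true divergence.

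**What to change.** In Section 9.1, specify a repeated-measures mixed model with time as a three-level factor, an unstructured 3x3 within-child covariance, REML and Kenward-Roger degrees of freedom. Alternatively, specify a paired T2–T0 comparison. State that the T2–T0 estimate and its 95% confidence interval come from the chosen analysis.

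The unstructured matrix has six parameters (three variances and three covariances), which is feasible with about 20 children. The change is to wording only. The price is about 19 instead of 38 error degrees of freedom: the critical t is 2.09 instead of 2.02, so the interval would be about 3% wider (2.09/2.02 = 1.03) if trajectories did not diverge at all.

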| **9.4** | **Statistical criteria for stopping the search:**  If the interim analysis at T1 showed a significant deterioration of the measures of functioning of the children |
| **9.5** | **Method of taking into account missing data:**  • To take into account the missing data we will use alternative sources of information. For example, in the case where the child does not realize an item (for lack of interest) this information will be collected from the child's parents or psychologists. This information should be verified on written accounts of volunteers or video recordings of play sessions. If there is missing data in one of the tests, the subject data concerning the test in question will be excluded from the analysis.  • In the case of premature termination of the method (unilateral decision of the family) tests will be made to estimate the evolution of the child, even outside the scheduled timing for assessments. If it is impossible to carry out these tests, we will be able to use the last films of the working sessions to rate CARS and Vineland. In all cases, those lost to follow-up will have to be taken into account in the interpretation of the results because they could constitute a bias (children progressing insufficiently being more likely to stop care prematurely). |
| **9.6** | **Change management at the initial statistical level**  A priori not applicable |
| **10** | **Right of access to data and source documents**  The right of access to the data and source documents will be strictly reserved to the investigator, to the collaborator of the investigator and to the person in charge of the quality control (cf §11) |
| **11** | **Quality control and quality assurance**  The investigator's collaborator will work under the control of the investigator. The relatively repetitive nature of the tests performed did not seem to require the intervention of a third party in quality control and quality assurance. |

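### Section 9.5 lets unflagged substitute reports and session films replace an instrument's planned source, so change over time may include a change of source

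*Protocol*

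**What the plan says.** Protocol 4.3 assigns a source to each instrument: PEP-R and imitation are administered to the child, and ADI-R, CARS and VABS come from the parents. Section 7.2 repeats this. For PEP-R it says "we will conduct a performance analysis based on an assessment and direct observation of the child". CARS and VABS are among the semi-structured parent interviews, of which it says "These are multidimensional assessments of learning and dysfunctions in everyday life".

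Section 9.5 sets three further rules:

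- **Unperformed items.** The rule is that "in the case where the child does not realize an item (for lack of interest) this information will be collected from" parents or psychologists. A check follows: "This information should be verified on written accounts of volunteers or video recordings of play sessions".
- **Families who leave.** Tests are to be made "even outside the scheduled timing for assessments". If that is impossible, "we will be able to use the last films of the working sessions to rate CARS and Vineland".
- **Exclusion.** "If there is missing data in one of the tests, the subject data concerning the test in question will be excluded from the analysis".

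Section 4.1 makes the imitation scale and the Vineland communication and socialization scores the main criteria. PEP-R imitation and verbal cognition, and CARS, are secondary.

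**The concern.** A comparison of T0, T1 and T2 measures change in the child only if each score is obtained in the same way each time. Under 9.5, some items or whole scores may come from a different source at one visit than at another, and no section asks for these values to be marked. The estimated change may then contain a change of source. There is no control group in which the same artefact would appear and could be subtracted. Section 4.4 instead relies on comparison with published data, which non-standard scoring weakens further.

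The substitute material comes largely from people who chose or deliver 3I: parents, volunteers' notes and films of 3I sessions. For imitation, failing to respond for lack of interest may itself be part of what is measured, most clearly in the spontaneous imitation subscale.

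Film rating can occur only in children who leave, and 9.5 expects children who progress too little to be the likelier leavers. Mode of measurement is therefore tied to prognosis.

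**Working it through.** The plan states no figure on this point, so there is none to reproduce. The check is a comparison of sections, followed by two illustrations on assumed inputs.

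**Step 1: planned source against substitute source.**

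| Instrument | Role (4.1) | Planned source (4.3, 7.2) | Substitute (9.5) |
| --- | --- | --- | --- |
| Imitation scale | main | child, in session | parents or psychologists, per item |
| Vineland communication, socialization | main | parent interview | last session films, dropouts only |
| PEP-R | secondary (imitation, verbal cognition) | child, in session | parents or psychologists, per item |
| CARS | secondary | parent interview | last session films, dropouts only |

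The item rule names no test. It speaks of the child not performing an item, which fits only the two child-administered tests.

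**Step 2: do other sections neutralise the switch?** Section 4.4 plans double coding and a kappa, but on the evaluation records. That addresses agreement between coders, not between sources. Section 4.2 describes assessments at a table in a room cleared of distractions, whereas the working films show ordinary play sessions. The last film is not tied to T1 or T2.

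**Step 3: bias in a mean item score.** Let s be the share of items substituted and c the share of those credited. Relative to observed-only scoring, the bias in change as a share of the maximum score is B = s(T2) × c(T2) − s(T0) × c(T0). All rates are assumed.

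- Equal refusal, rising credit: 0.15 × 0.70 − 0.15 × 0.40 = +0.045.
- Falling refusal, equal credit: 0.05 × 0.60 − 0.20 × 0.60 = −0.09.
- Equal refusal and equal credit: B = 0.

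The second line depends on the reference. If the child really can do 60% of the refused items, substitution is correct, and observed-only scoring shows a false gain of (0.20 − 0.05) × 0.60 = +0.09 from better cooperation alone.

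**Step 4: effect on a test.** Inputs from the protocol: n about 20 (9.2) and α = 0.05 (9.3). Assumed: a two-sided one-sample t-test on within-child change as a stand-in for the mixed model, no true change, and a source switch at one visit only that raises the change of k children by b SD of the change. The mean shift is k × b / 20. Rejection rates come from 200,000 simulated trials per row.

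| k of 20 | b (SD) | Mean shift (SD) | Rejection |
| --- | --- | --- | --- |
| 2 | 0.5 / 1 / 1.5 | 0.05 / 0.10 / 0.15 | 5.4% / 5.9% / 6.8% |
| 4 | 0.5 / 1 / 1.5 | 0.10 / 0.20 / 0.30 | 6.5% / 10.5% / 15.7% |
| 10 | 0.5 / 1 / 1.5 | 0.25 / 0.50 / 0.75 | 17.0% / 46.6% / 75.3% |

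For scale, the change detectable with 80% power at n = 20 is 0.66 SD. The effect therefore ranges from negligible to dominant, depending on inputs that the protocol does not give.

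**Step 5: consistency within 9.5.** One sentence fills gaps from other sources and another excludes the child's data for a test that has gaps. Nothing says which applies when. Exclusion also works against the mixed model of 9.1, which can use a child's other visits.

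**The case against.** The other side has several good points.

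- **Film rating is not the default for dropouts.** A reader might infer that it is. Section 9.5 puts off-schedule testing first, which already allows a VABS parent interview.
- **Parents are already the informants for CARS and VABS.** Their lack of independence is new only for the child-administered tests. Section 9.5 also asks for the substituted information to be verified, though against volunteers' accounts or session films.
- **The rater's ties are not established.** The 3I psychologist is trained in the method and approved by the sponsor (section 2), and sees the child weekly (4.5). But 9.5 does not say that this is the psychologist meant, or who would rate the films. Dependence on 3I is clear for much of the material, not for the rater.
- **Films may show part of what Vineland measures.** Interactive play can show some communication and socialization, the two main Vineland criteria. That films are useless for this purpose is not supported. What stands is that they are a different measurement from the planned interview.
- **Scoring every refusal as failure is no neutral remedy.** Step 3 shows that it can create a gain in favour of 3I when cooperation improves.

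These points narrow the concern but do not remove it. The protocol itself states a rule that changes the source of main-criterion scores and leaves the result unmarked.

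**Conclusion.** The point holds in a limited form. Section 9.5 conflicts with 4.3 and 7.2 on where scores come from, exposes both main criteria, and does not reconcile substitution with exclusion. Change over time may therefore include a change of source that a single-group study cannot detect.

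A reader might go further and infer that the results will be biased in favour of 3I, or that the bias is large. The documents support neither. They give no refusal rate, dropout rate or credit rate, so every number in steps 3 and 4 beyond n and α is an assumption, and the sign can go either way. The mean bias is zero if substitution is equally frequent and equally credited at all visits. Nothing in 9.5 ensures that balance, and film rating cannot be balanced because it arises only after a child leaves.

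**What to change.** Amend 9.5 as follows:

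1. In the primary analysis, use only scores from each instrument's planned source. Handle unperformed PEP-R and imitation items by the instrument's own scoring rule, identically at T0, T1 and T2.
2. Record substituted items and film-rated CARS and VABS in separate, flagged fields. Use them only in a sensitivity analysis, and report results under both rules.
3. Keep off-schedule testing, including the VABS parent interview, as the first resort for dropouts, as already planned.
4. Replace the exclusion sentence by keeping all available visits of every child in the mixed model. Without this step, a dropout whose VABS is left missing could fall out of the VABS analysis altogether.

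The cost is a change of wording and a flag in the data. There will be somewhat more missing data for dropouts, and the mixed model handles these well only if leaving is explained by scores already observed. Observed-only scores can also rise simply because cooperation improves, which is why both analyses should be shown.
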